**(R)-2-(4-((1,4-dioxan-2-yl)methoxy)phenyl)pyrimidin-4-yl)methanol (S-50).**

abbvie

10008519-2459 in DMSO d6 3mg  
Temp = 27 °C  
C16H18N2O4  
mrs400

Acq: VnmrJ VERSION 3.2 REVISION A/mrs400  
Proc: VnmrJ VERSION 3.2 REVISION A/m3001

Chemist: [name]  
Experiment: s2pul

nmr3471935

Oct 13 2017

Expected protons=18  
Whole protons observed=18  
Total integral =18.377

ID=82.20  
P =92.00

[figure not shown]

[figure not shown]

|               |      |             |                      |                 |              |                        |                     |
|---------------|------|-------------|----------------------|-----------------|--------------|------------------------|---------------------|
| Sample Name   | AO   | Position    | P2-C5                | Instrument Name | Instrument 1 | User Name              |                     |
| Inj Vol       | 0.1  | InjPosition |                      | SampleType      | Sample       | IRM Calibration Status | Success             |
| Data Filename | AO.d | ACQ Method  | IMSERC_ESI_Pos_Main_ | Comment         |              | Acquired Time          | 5/1/2018 6:10:04 PM |

[figure not shown]

File: ay31257x (13-Oct-2017 12:14:02)

Samp: 10008519-2459 MS-ay31257

Cmnt: LXQ/LC866450

Mode: +ESI

Base: 303.25

Formula: C16H18N2O4

Oper: AUTO

Intensity: 687447

Expected Mass: 302.13

Scan: 25,27 - 19,17

Client:

Score: 0.94

[figure not shown][figure not shown]

Date: Fri Oct 13 12:30:10 2017

Software: MSProcess 6.21

[figure not shown]

**Tert-butyl (7R,16R)-19,23-dichloro-10-[[2-(4-[[[(2R)-1,4-dioxan-2-yl]methoxy]phenyl]pyrimidin-4-yl)methoxy]-1-(4-fluorophenyl)-20,22-dimethyl-16-[(4-methylpiperazin-1-yl)methyl]-7,8,15,16-tetrahydro-18,21-etheno-13,9-(metheno)-6,14,17-trioxa-2-thia-3,5-diazacyclononadeca[1,2,3-cd]indene-7-carboxylate (S-51).**

10008519-2462 in DMSO \$20 BC504 5mg  
Temp = 27 C  
C57H59N6O9F1S1Cl2  
jr400

Expected protons=59  
Whole protons observed=58  
Total integral =62.008

Acq: VnmrJ VERSION 3.2 REVISION A/jr400  
Proc: VnmrJ VERSION 3.2 REVISION A/sasha

Chemist: [name]  
Experiment: s2pul

nmr3473918

Oct 20 2017

ID=81.70  
P =88.00

[figure not shown]

abbvie

10008519-2462-CARBON in DMSO \$22 BC2946 16mg  
Temp = 27 C  
C57H59N6O9F1S1Cl2  
mrs400

Acq: VnmrJ VERSION 3.2 REVISION A/mrs400  
Proc: VnmrJ VERSION 3.2 REVISION A/coffee

Chemist: [name]  
Experiment: s2pul

nmr3516669

Mar 23 2018

[figure not shown]

|               |      |             |                      |                 |              |                        |                     |
|---------------|------|-------------|----------------------|-----------------|--------------|------------------------|---------------------|
| Sample Name   | AP   | Position    | P2-C6                | Instrument Name | Instrument 1 | User Name              |                     |
| Inj Vol       | 0.1  | InjPosition |                      | SampleType      | Sample       | IRM Calibration Status | Success             |
| Data Filename | AP.d | ACQ Method  | IMSERC_ESI_Pos_Main_ | Comment         |              | Acquired Time          | 5/1/2018 6:13:08 PM |

[figure not shown]

File: ay41155x (20-Oct-2017 14:34:53)  
 Samp: 10008519-2462 MS-ay41155  
 Cmnt: LXQ/LC866450  
 Mode: +ESI Oper: AUTO  
 Base: 1093.68 Intensity: 1661857  
 Formula: C57H59N6O9F1Cl2 Expected Mass: 1092.34

Scan: 21,23 - 15,13

Client:

Score: 0.85

[figure not shown][figure not shown]

Date: Fri Oct 20 14:50:05 2017

Software: MSProcess 6.21

[figure not shown]

**(7R,16R)-19,23-dichloro-10-{{2-(4-{{(2R)-1,4-dioxan-2-yl)methoxy}phenyl}pyrimidin-4-yl)methoxy}-1-(4-fluorophenyl)-20,22-dimethyl-16-[(4-methylpiperazin-1-yl)methyl]-7,8,15,16-tetrahydro-18,21-etheno-13,9-(metheno)-6,14,17-trioxa-2-thia-3,5-diazacyclononadeca[1,2,3-cd]indene-7-carboxylic acid (ABBV-467).**

abbvie

10008519-2466-CARBON in DMSO \$30 BC2783 11mg  
Temp = 27 C  
C53H51N6O9F1S1Cl2  
mrs400

Acq: VnmrJ VERSION 3.2 REVISION A/mrs400  
Proc: VnmrJ VERSION 3.2 REVISION A/sasha

Chemist: [name]  
Experiment: s2pul

nmr3477791

Nov 2 2017

[figure not shown]

|               |      |             |                      |                 |              |                        |                     |
|---------------|------|-------------|----------------------|-----------------|--------------|------------------------|---------------------|
| Sample Name   | AQ   | Position    | P2-C7                | Instrument Name | Instrument 1 | User Name              |                     |
| Inj Vol       | 0.1  | InjPosition |                      | SampleType      | Sample       | IRM Calibration Status | Success             |
| Data Filename | AQ.d | ACQ Method  | IMSERC_ESI_Pos_Main_ | Comment         |              | Acquired Time          | 5/1/2018 6:16:10 PM |

[figure not shown]

File: ay51238x (30-Oct-2017 07:38:05)  
Samp: 10008519-2466-AFTER-DRYING MS-ay51238  
Cmnt: LXQ/LC866450  
Mode: +ESI Oper: AUTO  
Base: 1037.44 Intensity: 2130650  
Formula: C53H51N6O9F1S1Cl12 Expected Mass: 1036.28

Scan: 25,27 - 19,17

Client:

Score: 0.95

[figure not shown][figure not shown]

Date: Mon Oct 30 08:10:06 2017

Software: MSProcess 6.21

## **Phase 1 clinical trial**

**Inclusion/exclusion criteria.** Subjects must meet all of the following criteria in order to be included in the study. Anything other than a positive response to the questions below will result in exclusion from study participation.

### **Consent**

1. Subjects or their legally authorized representative must voluntarily sign and date an informed consent, approved by an independent ethics committee (IEC)/institutional review board (IRB), prior to the initiation of any screening or study-specific procedures.

### **Demographic and Laboratory Assessments**

2. At least 18 years old.
3. Eastern Cooperative Oncology Group (ECOG) performance status 0, 1, or 2.
4. Laboratory values meeting the following criteria during the screening period prior to first dose of study drug:
  - a. For subjects with AML, the following hematologic parameter requirements are not applicable. For subjects with MM, subjects must have adequate hematologic function, defined as follows:
  - b. Absolute neutrophil count  $\geq 1000/\text{mm}^3$ ;
  - c. Platelet count  $\geq 75,000/\text{mm}^3$ ;
  - d. Hemoglobin  $\geq 8 \text{ g/dL}$ ;
  - e. Serum alanine aminotransferase (ALT)  $\leq 2.5 \times$  upper limit of normal (ULN);
  - f. Serum aspartate aminotransferase (AST)  $\leq 2.5 \times$  ULN;
  - g. Total bilirubin  $\leq 1.5 \times$  ULN (subject with documented Gilbert's syndrome may have a total bilirubin  $>1.5 \times$  ULN);
  - h. Amylase  $\leq 2 \times$  ULN;
  - i. Lipase  $\leq 2 \times$  ULN;
  - j. Creatinine clearance (CrCl)  $\geq 60 \text{ mL/min}$ , measured by 24-hour urine collection or calculated using the Cockcroft-Gault formula.
5. Echocardiogram with ejection fraction  $\geq 50\%$  and no other clinically significant finding that would increase the subject's susceptibility to cardiac toxicity.

6. No clinically relevant or significant ECG abnormalities, including ECG with QT interval corrected for heart rate (QTc) using Fridericia's formula (QTcF) > 450 msec (males) or > 470 msec (females).
7. Willingness and ability to comply with procedures required in this protocol.

### **Disease Activity**

8. Documented diagnosis of MM (Parts A and B only).
9. For MM subjects only: measurable disease, defined as at least 1 of the following:
  - a. Serum monoclonal protein  $\geq 1$  g/dL
  - b. Urine M-protein  $\geq 200$  mg/24 hours
  - c. Serum immunoglobulin free light chain (FLC)  $\geq 10$  mg/dL (100 mg/L), provided serum FLC ratio is abnormal
10. For MM subjects only: Subjects who have relapsed after or are refractory or intolerant to all established MM therapies that are both known to provide clinical benefit, and locally available. At least 3 prior lines of therapy must have been administered (Appendix E), including 1 or more immunomodulatory agents (e.g., lenalidomide or pomalidomide), 1 or more proteasome inhibitors (e.g., bortezomib or carfilzomib), and 1 or more anti-CD38 monoclonal antibodies (e.g., daratumumab).
11. Documented diagnosis of AML (Parts C and D only; subjects with APL are excluded throughout the study).
12. AML subjects only: Total white blood cell count < 25,000/mm^3 (Note: hydroxyurea is permitted to meet this criterion).
13. For AML subjects only: failure to respond to, and/or relapse or progression after, at least 1 prior line of therapy, including all available standard therapies (per assessment of local investigator). Where applicable, this could include prior exposure to approved inhibitors of FLT3, IDH1, and IDH2.
14. No autologous stem cell transplant within 90 days prior to start of ABBV-467.
15. No allogeneic stem cell transplant within 180 days prior to start of ABBV-467.
16. No clinically significant graft versus host disease requiring ongoing systemic therapy.

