## Disease Activity

- ✓ 8. Documented diagnosis of MM (Parts A and B only).
- ✓ 9. For MM subjects only: measurable disease, defined as at least 1 of the following:
  - Serum monoclonal protein  $\geq 1$  g/dL
  - Urine M-protein  $\geq 200$  mg/24 hours
  - Serum immunoglobulin free light chain (FLC)  $\geq 10$  mg/dL (100 mg/L), provided serum FLC ratio is abnormal
- ✓ 10. For MM subjects only: Subjects who have relapsed after or are refractory or intolerant to all established MM therapies that are both known to provide clinical benefit, and locally available. At least 3 prior lines of therapy must have been administered ([Appendix E](#)), including 1 or more immunomodulatory agents (e.g., lenalidomide or pomalidomide), 1 or more proteasome inhibitors (e.g., bortezomib or carfilzomib), and 1 or more anti-CD38 monoclonal antibodies (e.g., daratumumab).
- ✓ 11. Documented diagnosis of AML (Parts C and D only; subjects with APL are excluded throughout the study).
- ✓ 12. AML subjects only: Total white blood cell count  $< 25,000/\text{mm}^3$  (Note: hydroxyurea is permitted to meet this criterion).
- ✓ 13. For AML subjects only: failure to respond to, and/or relapse or progression after, at least 1 prior line of therapy, including all available standard therapies (per assessment of local investigator). Where applicable, this could include prior exposure to approved inhibitors of FLT3, IDH1, and IDH2.
- ✓ 14. No autologous stem cell transplant within 90 days prior to start of ABBV-467.
- ✓ 15. No allogeneic stem cell transplant within 180 days prior to start of ABBV-467.
- ✓ 16. No clinically significant graft versus host disease requiring ongoing systemic therapy.

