### Multiple Myeloma Assessments

Disease assessments will be performed at the visits indicated in Section 2. MM subjects will be evaluated using the adapted International Myeloma Working Group (IMWG) 2016 criteria (see Section 7.3). Note that serum and urine for IMWG assessments do not need to be collected at C1D1 if the Screening samples were collected within 7 days of C1D1.

All subject's IMWG laboratory assessments (serum protein electrophoresis [SPEP], urine protein electrophoresis [UPEP], serum and urine immunofixation, serum free light chains, and serum quantitative immunoglobulins) will be performed by central laboratory, however, local labs may be performed at the investigator's discretion. All local laboratory results must be entered into the eCRF. Imaging and bone marrow assessments will be performed locally. Disease status should continue to be collected for MM subjects after study drug discontinuation for reasons other than disease progression.

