## Serum Free Light Chains

Blood samples for serum free light chain (FLC) testing will be collected for all subjects as outlined in Section 2.

Subjects with measurable disease in either SPEP and/or UPEP will be assessed for response only based on these 2 tests and not by the FLC assay. FLC response criteria are only applicable to fulfill the requirements of sCR or CR per IMWG criteria.

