| Complete response (CR)            | 
 
• Negative immunofixation on the serum and urine
 
• < 5% plasma cells in bone marrow aspirates
 
• Disappearance of any soft tissue plasmacytomas
 
                                                                                                                                                                                                                                                                                                                                                                                                                                                                                                                                                                 |
| Very good partial response (VGPR) | 
 
• Serum and urine M-protein detectable by immunofixation but not on electrophoresis, or
 
• ≥ 90% reduction in serum M-protein plus urine M-protein level < 100 mg per 24 hours
 
                                                                                                                                                                                                                                                                                                                                                                                                                                                                                                                                           |
| Partial response (PR)             | 
 
• ≥ 50% reduction of serum M-protein plus reduction in 24 hours urinary M-protein by ≥ 90% or to < 200 mg per 24 hours.
 
• If the serum and urine M-protein are not measurable, a ≥ 50% decrease in the difference between involved and uninvolved FLC levels is required in place of the M-protein criteria.
 
• If serum and urine M-protein are not measurable, and serum-free light assay is also not measurable, ≥ 50% reduction in plasma cells is required in place of M-protein, provided baseline bone marrow plasma-cell percentage was ≥ 30%.
 
• In addition to the above criteria, if present at baseline, a ≥ 50% reduction in the size (SPD) of soft tissue plasmacytomas is also required.
 
 |

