| Progressive disease c                                     | 
Any 1 or more of the following criteria:
 
 
• Increase of 25% from lowest confirmed response value in 1 or more of the following criteria:d 
 
• Serum M-protein (absolute increase must be <math>\geq 0.5</math> g/dL);
 
• Serum M-protein increase <math>\geq 1</math> g/dL, if the lowest M component was <math>\geq 5</math> g/dL;
 
• Urine M-protein (absolute increase must be <math>\geq 200</math> mg/24 hours);
 
• In subjects without measurable serum and urine M-protein levels, the difference between involved and uninvolved FLC levels (absolute increase must be <math>> 10</math> mg/dL);
 
• In subjects without measurable serum and urine M-protein levels and without measurable involved FLC levels, bone marrow plasma-cell percentage irrespective of baseline status (absolute increase must be <math>\geq 10\%</math>);
 
 
 
• Appearance of a new lesion(s), <math>\geq 50\%</math> increase from nadir in SPD of <math>> 1</math> lesion, or <math>\geq 50\%</math> increase in the longest diameter of a previous lesion <math>> 1</math> cm in short axis;
 
• <math>\geq 50\%</math> increase in circulating plasma cells (minimum of 200 cells per <math>\mu</math>L) if this is the only measure of disease
 
 |

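### Operations Manual 3.16 limits free light chain response criteria to sCR or CR, which conflicts with the FLC-based PR rule in Operations Manual 7.3 for myeloma subjects who enter on FLC alone

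*Protocol*

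**What the plan says.** **Entry.** Protocol 5.1, Disease Activity, criterion 9 reads "For MM subjects only: measurable disease, defined as at least 1 of the following". It then lists serum M-protein of at least 1 g/dL, urine M-protein of at least 200 mg/24 hours, and serum FLC of at least 10 mg/dL, "provided serum FLC ratio is abnormal". One of the three is enough. The synopsis and the eligibility list reproduced in the publication supplement say the same.

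**Assessment instruction.** Operations Manual 3.16, Serum Free Light Chains, has two sentences on use. The first concerns subjects measurable by SPEP and/or UPEP, who "will be assessed for response only based on these 2 tests and not by the FLC assay". The second is "FLC response criteria are only applicable to fulfill the requirements of sCR or CR per IMWG criteria". It does not say to whom it applies.

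**Criteria.** The head of 3.16 states: "MM subjects will be evaluated using the adapted International Myeloma Working Group (IMWG) 2016 criteria (see Section 7.3"). In the PR row of Operations Manual 7.3: "If the serum and urine M-protein are not measurable, a ≥ 50% decrease in the difference between involved and uninvolved FLC levels is required". The progressive disease row includes "In subjects without measurable serum and urine M-protein levels, the difference between involved and uninvolved FLC levels" among its measures.

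**Endpoints.** Protocol 3.2 counts PR in ORR and in CBR. Protocol 7.3 restricts DOR to subjects with PR or better.

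**The concern.** The second sentence of 3.16, taken as written, withdraws a criterion that the response table contains. An assessor who follows it would not use the FLC difference to award PR to a subject whose only measurable disease is FLC. An assessor who goes to Operations Manual 7.3 would. The same data could then be scored PR at one site and stable disease at another, in secondary endpoints that rest on about 20 subjects in Part B and on small dose cohorts in Part A. The error would run toward losing responders.

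The sentence is also inconsistent with the table in another respect. It ties FLC to sCR or CR, but the CR row has no FLC condition.

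**Working it through.** **1. Who is affected.** A subject with FLC of at least 10 mg/dL and an abnormal ratio, serum M-protein below 1 g/dL and urine M-protein below 200 mg/24 hours. Criterion 9 admits this subject.

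**2. That subject in the Operations Manual 7.3 table.**
- sCR: CR plus a normal FLC ratio and no clonal marrow cells. This is the only complete-response row with an FLC item.
- CR: negative immunofixation, under 5% marrow plasma cells, no soft tissue plasmacytoma. No FLC item.
- VGPR: M-protein only.
- PR: the "decrease in the difference between involved and uninvolved FLC levels is required in place of the M-protein criteria". This is the row that fits.
- PR by marrow plasma cells: allowed only when FLC is not measurable either, so closed to this subject.
- MR: M-protein only.
- Progressive disease: a 25% rise in the FLC difference with an absolute rise above 10 mg/dL.
- Stable disease: whatever meets none of the other rows.

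**3. The 3.16 sentence applied literally.** The FLC route to PR closes. The marrow route was never open, and VGPR and MR have no FLC alternative. A subject short of CR and not progressing falls to stable disease, and is lost from ORR, CBR and the DOR set. Progression is different: the sentence speaks of response criteria and does not mention progression, so that row stays in force.

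**4. The plan's own precision figures.** Table 5 gives exact one-sided 80% lower bounds for n = 20 response-evaluable subjects. With r responders the bound is the 0.20 quantile of Beta(r, 20 − r + 1).

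| r | Table 5 | Recomputed |
|---|---|---|
| 5 | 0.158 | 0.1584 |
| 6 | 0.201 | 0.2013 |
| 7 | 0.245 | 0.2454 |
| 8 | 0.291 | 0.2906 |
| 10 | 0.384 | 0.3840 |

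All five reproduce. The conflict changes no planned figure.

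**5. What a denied PR would do.** Each one costs 1/20 = 5 points of ORR. Protocol 7.3 plans a two-sided 90% exact interval, with lower limit the 0.05 quantile of Beta(r, 21 − r) and upper limit the 0.95 quantile of Beta(r + 1, 20 − r).

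| Responders | ORR | One-sided 80% bound | Two-sided 90% interval |
|---|---|---|---|
| 5/20 | 25% | 0.158 | 0.104 to 0.456 |
| 4/20 | 20% | 0.117 | 0.071 to 0.401 |
| 3/20 | 15% | 0.078 | 0.042 to 0.344 |

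Protocol 7.3 runs this analysis on all treated subjects. At the enrolment cap of 24, each denied PR costs 1/24 = 4.2 points.

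**6. Range over the unknown share.** Let f be the FLC-only share, assumed between 5% and 30%, with a true ORR of 30% (also assumed). In the worst case, where every FLC-only responder is denied, expected ORR is 0.30 × (1 − f): 28.5% at f = 5% and 21.0% at f = 30%. The binomial chance of at least 5 responders in 20 is 0.762 with none denied, 0.715 at f = 5% and 0.414 at f = 30%.

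**The case against.** The best defence is context. The disputed sentence directly follows one about subjects measurable by SPEP and/or UPEP, and can be read as stating what FLC is still used for in those subjects. If it covered everyone, the first sentence would have little point, since there would be no reason to single out SPEP/UPEP-measurable subjects. Section 3.16 also sends sites to Operations Manual 7.3, and the sentence itself defers to the IMWG criteria. Read that way, its limit on PR agrees with the table. This is probably what was meant. The limit is nevertheless not written, nothing in the paragraph says how FLC-only subjects are scored, and the mention of CR does not match the table on either reading.

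A reader might go further and infer that FLC-only subjects cannot be credited with PR at all, or that their progression has no laboratory rule. The documents do not support either. Operations Manual 7.3 gives an explicit FLC rule for PR and is named as governing, so the result is conflicting instruction, not impossibility. The progression rule is untouched, and lesion-based progression does not depend on FLC.

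The objection on size also stands. The share of FLC-only subjects is not given, and the loss arises only if an assessor applies the sentence literally to a subject who has responded. The 15% rate in Protocol 7.7 is an illustration in a study with no formal hypothesis test, so falling below it breaches no decision rule.

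**Conclusion.** The point holds as a conflict between two instructions in the Operations Manual. Criterion 9 admits FLC-only subjects. The second sentence of 3.16, as written, bars FLC from PR; Section 7.3 uses FLC to award it. The citation of CR is a further, smaller inconsistency.

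ORR, CBR and membership of the DOR set in Parts A and B are exposed. The size is 5 points of ORR per denied PR among 20, conditional on literal use of the sentence and on an FLC-only share that the documents do not report. It should not be presented as a measured bias, nor extended to the scoring of progression. No planned number is wrong, but the correction is worth making because response scoring should not depend on which of two sections an assessor follows.

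**What to change.** In Operations Manual 3.16, Serum Free Light Chains, replace the second sentence with wording to this effect: in subjects measurable by SPEP and/or UPEP, FLC is used only for the normal-ratio requirement of sCR; subjects without measurable serum and urine M-protein are assessed by the FLC criteria in Section 7.3. This removes the reference to CR and brings the paragraph into line with the table.

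The cost is a change to one sentence. Appendix D already schedules serum FLC for myeloma subjects at screening, Cycle 1 Day 1, Day 1 of each cycle and the Final Visit, so no sample or visit is added.

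This does not close a separate gap. The VGPR and MR rows have no FLC alternative, so FLC-only subjects lack a usable rule for either, and MR counts toward CBR. That needs its own decision in the Section 7.3 table.

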### **Subject History**

17. No unresolved clinically significant non-hematologic toxicity of  $\geq$  Grade 2 from prior anticancer therapy.
18. No history of acute or chronic pancreatitis.

19. No significant unresolved liver disease. Subjects with hepatitis C who have received definitive treatment and are considered cured will be eligible.
20. No known history of hepatitis B or HIV infection. Testing for hepatitis B and HIV are not required as part of Screening.
21. No major surgery within 4 weeks of study treatment.
22. No history of central nervous system involvement by underlying disease.
23. No history of plasma cell leukemia.

**Statistical analysis.** Efficacy and safety analyses were performed on the all-treated population, which comprises all subjects who received at least 1 dose of study drug. The PK population is defined as subjects who received at least 1 dose of study drug and have at least 1 valid post-baseline PK assessment; PK analyses were based on the PK population.

